### **13.9. Determination of sample size and randomization method**

Sample size is small as this is a preliminary pilot study and the first use in this patient group. Published rules of thumb for pilot studies recommend a sample size of 12 participants per arm completing the protocol [66]. To ensure this minimum number complete the protocol we will randomise 15 per arm to allow for 20% drop-out.

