### Feasibility

- Data on eligibility (proportion of patients assessed for eligibility deemed to be eligible and for each inclusion/exclusion criterion, proportion of patients eligible)
- Data on recruitment success (recruitment rate per month and week by week)
- Data on consent success (proportion of eligible patients consented)

- Assessment of randomization (evenness of numbers randomised to the two groups and balance of baseline characteristics between the two groups)
- Data on adherence to intervention (number of patients completing diary card, percentage compliance throughout treatment phase and reasons for missed doses)
- Data on retention to trial (number of patients completing final study assessment, reasons for discontinuation and number discontinuing in each case)
- Data on completeness of outcome measure reporting (for each outcome, number of patients with data available at each visit)

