## 5. STUDY DESIGN

### 5.1. Study description

This study aims to conduct a double-blind, randomised, parallel group, placebo-controlled phase II pilot trial of 35 days' duration with 400mg oral AZD4017 twice daily (n=15) or placebo (n=15) in patients with T2DM.

Eligible participants will be identified using medical records from the Diabetes Clinic at St. James' University Hospital (SJUH) by the CI or an authorised member of the direct care team. Once identified, patients will be invited to participate in the trial by email and/or post and provided with a Participant Information Leaflet (PIL) and PIL Feedback Form (returnable by self-addressed prepaid envelope).

Patients will be contacted by telephone to confirm willingness to participate and eligibility after 72 hours since sending the PIL.

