### **6.2. Estimated number of eligible participants**

Current data from the NIHR Yorkshire and Humber Clinical Research Network identified >45,000 patients with T2DM from 11 general practitioner (GP) practices, indicating a large target population pool. Therefore, we estimate a trial invitation requirement of 86 participants of whom an estimated 50% will consent and of whom an estimated 70% will be eligible (using the criteria below) to reach our target of 30 participants (allowing a 20% post-randomization drop-out rate to achieve a total of 24 completers with 12 in each arm).

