#### **6.4.3. Randomization process**

Treatment groups will be allocated on a fully randomised basis. A randomization schedule will be generated by the dedicated trials pharmacy representative who has signed/dated the staff delegation log and is not otherwise associated with this study. Patients will be randomised in a 1:1 treatment allocation ratio to either AZD4017 or placebo. The randomization schedule will be stored in a password protected file accessible only to the dedicated trials pharmacy (the CI and Scientific Lead will be blinded to the randomization process) until all samples have been collected.

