#### **6.5.2. Managing/replacing patients who withdraw early**

Participants who decide to withdraw will be invited to complete a withdrawal form which will be stored in the TMF (although refusal to do so will be respected). Participants who are withdrawn by the CI will be recorded in a Withdrawal Log that documents the enrolment number, participant initials, reason(s) for withdrawal and treatment offered (if applicable). A copy of the log will be retained in the CRF which will also directly capture information on withdrawal outcome (Discontinuation due to Adverse Event or Elective Withdrawal). Withdrawal Log originals will be stored in the TMF. Participants who withdraw or are withdrawn pre-randomization will be classified as screening failures (see section 6.3.4). Participants who withdraw or are withdrawn post-randomization (see section 6.5) will be classified as withdrawals and will not be replaced.

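### Randomising 15 per arm makes 12 completers per arm the expected number, not an ensured minimum, and the stated allocation method does not by itself give 15:15

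*Protocol*

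**What the plan says.** Section 13.9 gives the only justification for the sample size: "Published rules of thumb for pilot studies recommend a sample size of 12 participants per arm completing the protocol". It continues: "To ensure this minimum number complete the protocol we will randomise 15 per arm to allow for 20% drop-out". Section 6.2 gives the same numbers in softer terms, "allowing a 20% post-randomization drop-out rate to achieve a total of 24 completers with 12 in each arm". Under section 6.5.2, participants who leave after randomisation "will be classified as withdrawals and will not be replaced".

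On arm sizes, section 5.1 describes "400mg oral AZD4017 twice daily (n=15) or placebo (n=15) in patients with T2DM".

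On allocation, section 6.4.3 says: "Treatment groups will be allocated on a fully randomised basis". It adds a 1:1 ratio and a schedule generated by the trials pharmacy, but names no blocking or other restriction. Section 13.9 has the randomisation method in its heading and describes none. The feasibility list in section 4.2 includes "evenness of numbers randomised to the two groups and balance of baseline characteristics between the two groups" among the things to be assessed.

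**The concern.** Section 13.9 treats 12 completers per arm as a floor that the design secures. Dividing 12 by the planned retention secures it only on average, and without replacement nothing recovers a shortfall. As this is the sole stated basis for the size, the protocol claims a property that the design does not have.

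The second problem feeds the first. The arm sizes are stated as fixed, but the method as worded could be followed to the letter by a pharmacy list that does not produce them. Uneven arms lower the chance that the smaller one reaches 12. They also matter at the first safety review (section 13.8), held after 8 patients have reached day 35 or been withdrawn, where safety values are shown by treatment group.

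**Working it through.** **Inputs.** Target of 12 completers per arm, 15 randomised per arm and 20% drop-out (13.9); 30 in total (6.2); 1:1 ratio (6.4.3); no replacement (6.5.2). Assumptions that the protocol does not state: drop-out is independent between participants, has the same rate in both arms, and is truly 20% in the base case.

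**1. The plan's own figures reproduce.**
- 12 / (1 − 0.20) = 15.0 per arm.
- 30 × 0.80 = 24 completers.
- 86 invited × 0.50 × 0.70 = 30.1 participants (6.2).

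**2. Arms fixed at 15:15, drop-out 20%.** Completers in one arm follow Bin(15, 0.8):
- P(12) = 455 × 0.8¹² × 0.2³ = 0.250
- P(13) = 105 × 0.8¹³ × 0.2² = 0.231
- P(14) = 15 × 0.8¹⁴ × 0.2 = 0.132
- P(15) = 0.8¹⁵ = 0.035

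The sum is 0.648 for one arm. For both arms, 0.648² = 0.420.

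**3. Simple 1:1 randomisation of 30, drop-out 20%.** Sum over the size a of one arm: Σ C(30, a) × 0.5³⁰ × P(Bin(a, 0.8) ≥ 12) × P(Bin(30 − a, 0.8) ≥ 12) = 0.215.

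**4. Arm sizes under simple randomisation.**
- P(exactly 15:15) = C(30, 15) × 0.5³⁰ = 0.144.
- P(both arms start with at least 12) = 0.800, so one arm begins below 12 in 20% of cases before anyone drops out.

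**5. Sensitivity to the drop-out rate.** Probability that both arms reach 12 completers:

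| True drop-out | Fixed 15:15 | Simple randomisation of 30 |
|---|---|---|
| 10% | 89.2% | 53.6% |
| 15% | 67.7% | 36.8% |
| 20% | 42.0% | 21.5% |
| 25% | 21.3% | 10.5% |

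**6. What near-assurance would take, for scale only.** At 20% drop-out with equal arms, 16, 17 and 18 per arm give 63.7%, 80.0% and 90.0%.

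**7. The 8-patient review.** Taking the 8 as a random split under simple randomisation, P(one arm has 2 or fewer) = 2 × (1 + 8 + 28)/256 = 28.9%, and P(one arm has 0 or 1) = 2 × (1 + 8)/256 = 7.0%. With permuted blocks of 2, 4 or 6, the first 8 randomised end a block or stand at position 2 or 4 within one. The arms then differ by at most 2, so the split is no worse than 3:5. The first 8 to reach day 35 or withdraw need not be exactly the first 8 randomised, so this is approximate for the review itself.

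**The case against.** The strongest reply is that there is no arithmetic error. Inflating 12 by the expected drop-out is ordinary practice, and section 6.2 already words it as an allowance. That stands: 15 is correctly computed. What fails is the claim in 13.9 that it ensures a minimum.

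A reader might go further and say that the design succeeds only about one time in five. The protocol does not support this as a headline. It needs simple randomisation, which the wording in 6.4.3 and the evenness item in 4.2 suggest but do not state. That wording could also mean only that allocation is not stratified or minimised, a list prepared in advance can be balanced exactly, and evenness could be reported under blocking too. Sections 5.1 and 13.9 fix 15 per arm, for which the figure is 42%. Both figures also treat the 20% allowance as the true rate, and the protocol reports no observed rate.

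Blocking may be specified in a pharmacy document or an analysis plan that is not shown, so its absence alone is no fault. The fault is that the protocol's own statements on method and arm sizes do not fit together as written.

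Two further inferences should be resisted. Uneven arms hardly widen the primary interval: at 12:18 against 15:15 with equal variances, √(1/12 + 1/18) / √(2/15) = 0.373/0.365 = 1.02. Nor is one arm likely to be almost empty at the 8-patient review: 0 or 1 patient occurs in 7% of cases even under simple randomisation, and 13.8 provides for later looks.

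The consequences are limited in any case. The analysis is descriptive with no formal test (13.2). Participants withdrawn from study drug may complete the assessments (6.5), and non-compliance is not a ground for withdrawal (8.9.1). The primary measure is at day 28, and multiple imputation will be attempted (13.7). Loss of a completer is therefore not always loss of primary data.

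**Conclusion.** The point holds as a correction to a stated property and a reconciliation of sections 5.1, 6.4.3 and 13.9. At the plan's own 20% drop-out, the chance that both arms reach 12 completers is below one half on either reading of allocation: about 42% with 15:15 fixed and about 21% under simple randomisation. Over true drop-out rates of 10% to 25%, the ranges are 89% to 21% and 54% to 10%. All these figures assume independent drop-out at the same rate in both arms.

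The impact is modest. Twelve per arm is a rule of thumb, no power is claimed, and falling one or two short breaks no stated error rate. The documents do not support reading this as a failed sample size or as a reason to enlarge the trial.

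**What to change.** - **Section 13.9:** replace the claim of ensuring 12 completers with a statement of expectation, for example: *randomising 15 per arm gives an expected 12 completers per arm at 20% drop-out; if drop-out is independent, the probability that both arms reach 12 is about 42%.*
- **Sections 6.4.3 and 13.9:** state that the pharmacy list is restricted so that 30 allocations total 15:15, for example by permuted blocks of varying size with the sizes withheld from investigators. The particular block sizes are a matter of choice. Replace or explain the present allocation wording so that it agrees with section 5.1.

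Such a list delivers the stated arm sizes, removes the lower of the two probabilities as a possible reading, and keeps the arms close to even at the 8-patient safety review. It does not raise the chance above 42% at 20% drop-out, which is why the wording must change as well.

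The cost is a reworded sentence in 13.9, a short statement of the allocation method, and a list-generation setting in pharmacy before the first patient is randomised. No extra patients are requested.

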#### **13.10. Procedure for unblinding the study prior to analysis**

The final database is not to be locked or unblinded until a review of the data has been completed, the per protocol sample identified, and the statistical analysis plan has been finalised. The dates of each of these milestones will be recorded in the study documentation prior to the full unblinding of the data.

## **14. ETHICS AND REGULATORY REQUIREMENTS**

### **14.1. Good Clinical Practice**

This study will be conducted in accordance with applicable laws and regulations including, but not limited to, the ICH Guideline for GCP and the recommendations guiding ethical research involving human subjects adopted by the 18th World Medical Assembly, Helsinki, Finland, 1964, amended at the 48th General Assembly, Somerset West Republic of South Africa, October 1996. The REC and MHRA must review and approve the protocol and Informed Consent Form before any subjects are enrolled. Before any protocol-required procedures are performed, the subject must sign and date the REC-approved Informed Consent Form. The right of a patient to refuse participation without giving reasons must be respected. The patient must remain free to withdraw at any time from the study without giving reasons and without prejudicing his/her further treatment. The study will be submitted to and approved by a Main REC and the appropriate regulatory authorities prior to entering patients into the study.

## 14.2. Delegation of Investigator duties

The Investigators will ensure that all persons assisting with the trial are adequately qualified and informed about the protocol, any amendments to the protocol, the study treatments, and their trial-related duties and functions.

The Scientific Lead will maintain a delegation log of co-Investigators and other appropriately qualified persons to whom he or she has delegated significant trial-related duties.

## 14.3. Subject information and informed consent

Before being enrolled in the clinical study, subjects must consent to participate after the nature, scope, and possible consequences of the clinical study have been explained in a form understandable to them.

A PIL that includes information about the study will be prepared and given to the subject at least 24 hours prior to the screening visit. This document will contain all the elements required by the ICH E6 Guideline for GCP and any additional elements required by local regulations. The document must be translated (by an independent interpreter) into a language understandable to the subject and must specify who informed the subject. Where required by local law, the person who informs the subject must be a physician.

During verification of eligibility, patients will be given the opportunity to ask questions and the nature and objectives of the study will be explained. A research nurse may help in this process but the study doctor is responsible for the General Informed Consent discussions at the Screening Visit. The Skin Biopsy Informed Consent at Visits 1 and 4 can be received by a qualified member of staff who has signed/dated the staff delegation log (i.e. study doctor or research nurse).

After reading the informed consent document, the subject must give consent in writing. The subject's consent must be confirmed at the time of consent by the personally dated signature of the subject and by the personally dated signature of the person conducting the informed consent discussions, (i.e. the study doctor for General Informed Consent or qualified research nurse for Skin Biopsy Informed Consent).

The original signed Informed Consent Form will be retained in the TMF. Other copies of the consent form are required:

- One copy will be kept in the patient's clinical notes
- One copy will be given to the patient

Consent is an ongoing process and will be reassessed at each study visit.

The Scientific Lead will not undertake any measures specifically required only for the clinical study until valid consent has been obtained.

The CI must inform the subject's GP about the subject's participation in the trial if the subject has a GP and if the subject agrees to the GP being informed.

#### **14.4. Subject confidentiality**

Only the subject enrolment number will be recorded in the CRF, and if the subject name appears on any other document (e.g. laboratory report), it must be obliterated on the copy of the document to be supplied to anyone outside the clinical care team. The subjects will be informed that representatives of the Sponsor, REC or regulatory authorities may inspect their medical records to verify the information collected, and that all personal information made available for inspection will be handled in strictest confidence.

All information collected during the course of the trial will be kept strictly confidential.

Information will be held securely on paper and electronically.

The Diabetes Clinic at SJUH and LMBRU at CAH will comply with all aspects of the Data Protection Act 1998.

The Scientific Lead will maintain a personal subject identification list (subject numbers with the corresponding subject names) to enable records to be identified.

#### **14.5. Subject identification cards**

All patients who receive at least one dose of study medication will be issued with identification cards which state the name of the IMP and an indication of the possibility that the patient may be receiving placebo or control treatment, in addition to details of whom to contact in the event of an emergency.

#### **14.6. Approval of clinical study protocol and amendments**

Before the start of the study, the clinical study protocol, informed consent document, and any other appropriate documents will be submitted to the REC, the MHRA and the Sponsor with a cover letter or a form listing the documents submitted, their dates of issue, and the site (or region or area of jurisdiction, as applicable) for which approval is sought. If applicable, the documents will also be submitted to the authorities, in accordance with local legal requirements.

Investigational products can only be supplied to the Sponsor after documentation on all ethical and legal requirements for starting the study has been received by the product provider.

Before the first subject is enrolled in the study, all ethical and legal requirements must be met, including approval of the study by the NHS, the Sponsor Research and Development department, the REC and the MHRA.

Amendments must be evaluated to determine whether formal approval must be sought and whether the informed consent document should be revised, thus all protocol amendments and administrative changes must first be discussed with and approved by the Sponsor before being submitted to the REC and the MHRA, in accordance with legal requirements.

The Scientific Lead must keep a record of all communication with the REC, the MHRA, and the Sponsor. This also applies to any communication between the Scientific Lead and the authorities.

#### **14.7. Protocol amendments**

Requests for any amendments to the study must be sent to the Sponsor by the Scientific Lead. The Sponsor will determine whether said amendments are substantial or non-substantial prior to their submission to the appropriate bodies for approval. Patients will be re-consented to the study if the amendments affect the information they have received, patient safety, or if the change alters the type or quality of the data collected for the study. Patients will only be re-consented AFTER an amendment has been fully approved.

#### **14.8. Ongoing information for MHRA/REC**

Unless otherwise instructed by the MHRA, REC and the Sponsor, the Scientific Lead must submit to the MHRA, REC and the Sponsor:

- Information on SUSAR from the CI's site, as soon as possible and within 24 hours (one business day) of the research team becoming aware of them
- Expedited safety reports, as soon as possible
- Annual reports on the progress of the study
- The Declaration of the End of a Trial form

### **15. FINANCE AND INSURANCE**

#### **15.1. Indemnity and insurance**

The University of Leeds is able to provide insurance to cover for liabilities and prospective liabilities arising from negligent harm. In certain circumstances we provide insurance cover for claims arising from non-negligent harm. Clinical negligence indemnification will rest with the participating NHS Trust or Trusts under standard NHS arrangements.

Further details of liability and insurance provisions for this study are given in separate agreements.

#### **15.2. Financial disclosure**

None of the Investigators or members of the research team have any financial involvement with the sponsorship or funding bodies or will receive personal benefits, incentives or payment over and above normal salary.

### **16. PUBLICATION**

According to the GC-SHealD Research Collaboration Agreement with AstraZeneca, the University of Leeds and its employees, students and agents shall be entitled to publish the results of, or make presentations related to, this study to the extent that such publications or presentations are consistent with academic standards, are not false or misleading, and are not for commercial purposes, subject to the following:

The University of Leeds shall provide, or shall ensure that the Scientific Lead provides, AstraZeneca with copies of any materials relating to the study, study data or the developed technologies that it either intends to publish (or submit for publication, including, but not limited to, materials to be posted on clinical trial registries) or make any presentations relating to, at least forty five days in advance of publication, submission or presentation.

